The response rate is the rate of patients whose best overall response {3.8(6) Best overall response} in a target population with measurable lesions is CR or PR as a proportion of all the cases that underwent treatment.

(7) Health-related quality of life (HRQoL)

See "5.5 Survey of health-related quality of life".

(8) Adverse events (toxicity)

Adverse events that are observed from registration to the discontinuation of the protocol treatment will be evaluated in all treated cases (see "19 Evaluation and reporting of adverse events").

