## 5.4 Survey

### (1) Survey items

The following survey and examination will be implemented to evaluate the efficacy and safety of the protocol treatment for subjects in this study.

- ① Medical history
- ② Physical findings
- ③ Diagnostic imaging for evaluation of breast cancer focus
- ④ Survey of adverse events
- ⑤ Treatment survey: the name of the selected medicine and the reasons for the selection, compliance, combined medicine, and treatment
- ⑥ Survey of health-related quality of life (HRQoL)
- ⑦ Survey of aftertreatment
- ⑧ Prognosis survey

The following section, 5.4 (2), specifies the guidelines for conducting surveys ①–⑤ within the range of regular clinical practice while paying careful attention to the burden imposed on patients in this study. In addition, survey of HRQoL will be implemented with attention to the burden imposed on the study subjects. Usually, the time for each survey is limited to 15 minutes and the number of times the survey is carried out is limited to the requisite minimum (3 times in total including at the time of registration, and 1 and 3 months after the initiation of protocol treatment). Surveys at 6 months after the initiation of protocol treatment and later will not be implemented except for the surveys of aftertreatment and prognosis.

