**(5) Survey planned at 3 months after the initiation of protocol treatment**

The following survey will be implemented at 3 months after the initiation date of protocol treatment:

① Physical findings

\* It is acceptable to implement the survey within 2 weeks before or after the specified day.

- A) Weight
- B) Performance status

② Diagnostic imaging for evaluation of breast cancer lesions

\* It is desirable to use the same techniques as those used for the examination implemented before registration.

\* It is recommended to implement the examination within 2 weeks before or after the specified day.

- A) Chest CT, MRI, or chest X-ray
- B) Abdominal CT, MRI, or abdominal ultrasound
- C) Bone scintigraphy when bone metastasis is clinically suspected
  - \* When bone metastasis is suspected by bone scintigraphy, bone radiography, CT, or MRI, etc. is conducted to further evaluate the lesion.
- D) Brain CT or MRI when brain metastasis is clinically suspected
- E) Evaluation and recording of lymph nodes and locally recurrent skin foci
  - \* Inspection: It is favorable to record progress using photographs with indicators attached.
  - \* Palpation: The size of foci such as superficial lymph nodes and cutaneous metastases will be directly measured from outside the body if their sizes are measurable. It is desirable to use CT and/or ultrasound for evaluations where applicable.

③ Survey of adverse events

The presence or absence of adverse events of Grade 3 or higher occurring within the past 3 months will be confirmed and recorded.

\* It is acceptable to implement the survey within 2 weeks before or after the specified day.

The contents of survey are the same as specified in ④ of 5.4 (3). The survey must be completed before registration.

④ Survey of treatment state

- A) Presence or absence of discontinuation of the protocol treatment and the reasons and date of discontinuation if discontinued
- B) Compliance with the protocol treatment for the past 3 months

- C) Presence or absence of use of bisphosphonate formulation or anti-RANKL antibody for the past 3 months
  - D) Presence or absence and reasons for implementation of concomitantly used therapies (surgical therapy for breast cancer focus, radiotherapy for breast cancer focus, any molecularly-targeted drugs other than mTOR inhibitors, chemotherapy, immunotherapy, other drugs recognized to have antitumor activity against breast cancer) for the past 3 months
- ⑤ Survey of HRQoL {the same as 5.4 (4) ①}

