- (6) Survey plan at 6 months after the initiation of protocol treatment
- The following survey will be implemented at 6 months after the initiation day of protocol treatment:
- \* However, the survey at 6 months after the initiation is not required when discontinuation of the protocol treatment or progression is reported in the survey at 3 months after the initiation. Move to the survey detailed in (7) for such cases.
- ① Physical findings
- \* It is acceptable to implement the survey within 2 weeks before or after the specified day.
- A) Weight
  - B) Performance status
- ② Diagnostic imaging for evaluation of breast cancer lesions
- \* It is desirable to use the same techniques as those used for the examination implemented before registration.
- \* It is recommended to implement the examination within 2 weeks before or after the specified day.
- A) Chest CT, MRI, or chest X-ray
  - B) Abdominal CT, MRI, or abdominal ultrasound
  - C) Bone scintigraphy when bone metastasis is clinically suspected
    - \* When bone metastasis is suspected by bone scintigraphy, bone radiography, CT, or MRI, etc. will be conducted to further evaluate the lesion.
  - D) Brain CT or MRI when brain metastasis is clinically suspected
  - E) Evaluation and recording of lymph nodes and locally recurrent skin foci
    - \* Inspection: It is favorable to record progress using photographs with indicators attached.
    - \* Palpation: The size of foci such as superficial lymph nodes and cutaneous metastases will be directly measured from outside the body if their sizes are measurable. It is

desirable to use CT and/or ultrasound for evaluations where applicable.

③ Survey of adverse events

The presence or absence of adverse events of Grade 3 or higher occurring between the previous survey and the day of the current survey is confirmed and recorded.

\* It is acceptable to implement the survey within 2 weeks before or after the specified day.

The contents of survey are the same as specified in ④ of 5.4 (3). The survey must be completed before registration.

④ Survey of treatment state

- A) Presence or absence of discontinuation of the protocol treatment and the reasons and date of discontinuation if discontinued
- B) Compliance with the protocol treatment for the past 3 months
- C) Presence or absence of use of bisphosphonate formulation or anti-RANKL antibody for the past 3 months

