- D) Presence or absence and reasons for implementation of concomitantly used therapies (surgical therapy for breast cancer focus, radiotherapy for breast cancer focus, molecularly-targeted drugs other than mTOR inhibitors, chemotherapy, immunotherapy, other drugs recognized to have antitumor activity against breast cancer) for the past 3 months

(7) Survey plan at 6 months or later after the initiation of protocol treatment or after discontinuation of the protocol treatment

① Timing of survey

- A) Every year from 6 months after the initiation of the protocol treatment when the protocol treatment is ongoing at the time of 6 months after the initiation of the protocol treatment
- B) Every year from the day of discontinuation of the protocol treatment when the protocol treatment is discontinued at the time of 6 months after the initiation of the protocol treatment

② Contents of survey

- A) Continuation state of protocol treatment: Presence or absence of continuation of the protocol treatment. If it is discontinued, the date and reasons for the discontinuation {only for subjects corresponding to the criteria specified in 5.4 (7) ①-A)}.
- B) Survey of progression: Presence or absence of progression defined in 3.9 (2). When progression was observed, the date when the progression occurred was determined (not required for a subject whose progression is already reported.)

- C) Survey of after-treatment: Presence or absence of implementation of chemotherapy. If chemotherapy is implemented, the date and type of chemotherapy.
- D) Survey of prognosis: The final confirmed day of survival. In case of death, the date and cause of death.

(8) Discontinuation of survey

When a case meets one of the following criteria, the survey will be discontinued.

- ① When it is determined that continuation of the rest of the survey is not possible due to changing hospital or other reasons
- ② Withdrawal of consent
- ③ Death
- ④ When it becomes clear that the eligibility criteria are not satisfied
- ⑤ Other reasons, when it is determined that continuation of the study as a subject is not possible

---

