### (3) Progress report: During protocol treatment

At 3 and 6 months after the initiation of protocol treatment unless discontinued.

No report at 6 months is required when discontinuation of the protocol treatment is reported in the survey at 3 months.

- ① Body weight, PS
- ② Implementation state of image examinations after the initiation of protocol treatment: 5.3.4 (2) and 5.3.5 (2)
- ③ Focal findings: Descriptions of the site and measurement results for target lesions and non-target lesions.
- ④ Adverse events
- ⑤ Concomitant drugs and treatment, and reasons for implementation
- ⑥ Presence or absence of discontinuation of the protocol treatment. When the treatment is discontinued, the reasons for the discontinuation and date of discontinuation.
- ⑦ Compliance of the protocol treatment
- ⑧ Time point response

(4) Progress report: After-treatment

- ① After-treatment survey: Implementation date and type of chemotherapy

(5) Progress report: Prognosis survey

- ① Presence or absence of progression and date of confirmation  
② Date of last confirmation of survival, date and cause of death (in case of death)

(6) Emergency adverse event report

(See Appendix E)

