#### (1) Evaluation duration of adverse events

The evaluation duration of adverse events in this study is from the registration to 30 days after the completion of the protocol treatment specified as the object of evaluation.

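### The protocol gives two different end-points for the adverse event window, and routine collection stops at about month 6, so the planned incidence covers neither window for patients treated longer.

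*Protocol*

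**What the plan says.** **Two windows for one outcome.** Section 3.9 (8) defines the outcome: "Adverse events that are observed from registration to the discontinuation of the protocol treatment will be evaluated in all treated cases". It refers the reader to Section 19, where 19.1 (1) sets the evaluation period as "from the registration to 30 days after the completion of the protocol treatment specified as the object of evaluation". Both start at registration; they differ in where they end.

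**Collection.** The schedule in Section 5.4 (2) places adverse event surveys before registration and at 3 and 6 months.
- The 3-month survey looks back over the treatment period so far: "The presence or absence of adverse events of Grade 3 or higher occurring within the past 3 months will be confirmed and recorded". The 6-month survey covers the time since the previous one.
- Section 5.4 (1) then closes routine collection: "Surveys at 6 months after the initiation of protocol treatment and later will not be implemented except for the surveys of aftertreatment and prognosis". Read literally, this would drop the 6-month survey too. The schedule and Section 5.4 (6) show that it is meant to take place, so I read the sentence as applying after it.
- Section 5.4 (6) says the 6-month survey "is not required when discontinuation of the protocol treatment or progression is reported in the survey at 3 months after the initiation". Section 5.7 (3) has a narrower waiver: "No report at 6 months is required when discontinuation of the protocol treatment is reported in the survey at 3 months".
- Section 5.4 (7) continues "Every year from 6 months after the initiation of the protocol treatment when the protocol treatment is ongoing" at month 6. Its contents are treatment status, progression, chemotherapy and survival.

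**Reporting routes.** Section 19.2 (2) makes every Grade 3 or 4 event that is not urgent a regular reporting obligation, with no time limit. Section 19.2 (3) sends those events on the Progress report at its normal submission time, and Section 5.6 makes the adverse event Progress report due only for the 3- and 6-month surveys. Urgent reports under Section 19.2 (1) cover deaths and unknown non-hematological toxicity and are not tied to survey dates.

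**Analysis.** Section 5.10 (3) plans incidence by type and grade in all treated cases.

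**The concern.** Safety is half of objective (1). Both stated windows run to the end of treatment or beyond, so a reader of the results would take the incidence as covering time on treatment. The data stop earlier. A patient who stays on treatment past month 6 can have a routine Grade 3-4 event that falls inside both windows and has no scheduled form to be entered on.

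The same gap reaches oversight. Section 19.3 (2) has the research representative pass reportable events, regular as well as urgent, to the independent data monitoring committee. A regular event after month 6 has no scheduled report to start that chain.

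A statistical analysis plan can choose between the two windows, but it cannot recover events that were never collected.

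**Working it through.** The plan gives no figure for adverse event coverage, so there is none to reproduce. The check sets each type of patient against the two windows.

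**Coverage by time of stopping**

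| Patient | To discontinuation (3.9 (8)) | To 30 days after completion (19.1 (1)) |
|---|---|---|
| Stops by the 3-month survey | Covered from treatment start by the 3-month look-back | Tail complete only if treatment stopped about 30 days or more before that survey, roughly by month 2 |
| Stops between the 3- and 6-month surveys | Covered by the 6-month survey | Tail complete only if treatment stopped by about month 5 |
| Progression reported at month 3, treatment continues | Not covered after month 3 under the waiver in 5.4 (6) | Not covered after month 3 |
| Treated beyond month 6 | Not covered after month 6 | Not covered after month 6 |

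The loss under both windows therefore comes from patients treated beyond month 6, plus the smaller group in the third row. Patients who stop earlier lose at most part of the 30-day tail.

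**Illustrative size**

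Inputs: the enrolment target of at least 200 (Section 7.3), and the share S still on treatment at month 6. The protocol does not give S. I take 30% to 50%, borrowing the threshold and expected clinical benefit rates in Section 7.3. This is an assumption: clinical benefit means freedom from progression for 6 months, not being on treatment.

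*Window to discontinuation.* Patients not fully covered = S × 200.
- S = 0.30: 0.30 × 200 = 60
- S = 0.50: 0.50 × 200 = 100

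*Window with the 30-day tail.* This also needs a shape for time on treatment, T. I assume it is exponential with rate λ = −ln(S)/6 per month. Thirty days is 30/30.4375 = 0.986 months. With the 6-month survey waived for those who stop by month 3, a patient is fully covered if T ≤ 3 − 0.986 = 2.014, or if 3 < T ≤ 6 − 0.986 = 5.014. So

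P(covered) = 1 − exp(−2.014λ) + exp(−3λ) − exp(−5.014λ).

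- S = 0.30: λ = 0.2007; P = 0.333 + 0.548 − 0.366 = about 0.514; not fully covered = 200 × 0.486 = about 97
- S = 0.50: λ = 0.1155; P = 0.208 + 0.707 − 0.560 = about 0.354; not fully covered = 200 × 0.646 = about 129

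A simulation of the same model gives the same counts. In it, the unobserved share of window time is 30-50% to discontinuation and about 32-51% with the tail. The model leaves out patients who progress by month 3 and stay on treatment.

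**The case against.** The best defence is that light collection is deliberate. The study is observational, Section 5.4 (1) openly limits the surveys to spare patients, Section 19.1 (2) restricts collection to Grade 3 and above, and Section 5.10 promises incidence only for reported events. Deaths and unknown non-hematological toxicity still arrive by urgent report, so late capture is selective rather than nil. The adverse event Progress report may be submitted up to 2 months after the survey date, so the form can still be open during the 30 days after a stop close to month 3. The form itself (Appendix D) is not shown.

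This defends a 6-month limit on collection. It does not defend two conflicting windows that both run past that limit. The open form eases the tail for some patients but does nothing for those treated beyond month 6.

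Three stronger readings are tempting, and the documents do not support them:
- *Patients who stop early for toxicity lose the most information.* They do not. The 3-month look-back covers them from treatment start to discontinuation.
- *Cohorts with longer treatment will look safer than they are.* This is not shown. The cut-off applies to every cohort, and up to month 6 longer treatment contributes more observed exposure, which can raise counted incidence. Section 7.3 also says the study does not aim to compare cohorts.
- *Half of the patients are affected, or at most half.* The protocol gives no share on treatment at month 6. The clinical benefit rate is only a proxy, and the rates cited in Section 7.2 run from 12% to 79.6%.

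**Conclusion.** The point holds as an inconsistency between the stated outcome and the data that will exist. Sections 3.9 (8) and 19.1 (1) end the window at different times, and routine collection ends at the 6-month survey, or at the 3-month survey where the later one is waived. Incidence in all treated cases cannot cover either window for patients treated beyond month 6, or, under Section 5.4 (6), for those with progression reported at month 3 who stay on treatment.

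At an assumed 30-50% on treatment at month 6, that is 60-100 of 200 patients under the shorter window. Under the longer one it is about 97-129, which also rests on the exponential assumption; most of those added lose only part of the 30-day tail. No direction of bias between cohorts has been established. The change should be made: it is cheap, and without it the reported incidence would not match its own definition.

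**What to change.** 1. Reconcile Sections 3.9 (8) and 19.1 (1) to a single window. Keep registration as the start, since both agree on it, and let the window end no later than the patient's last adverse event survey.
2. In Section 5.10, label the incidences as Grade 3 or higher events up to the 6-month survey, or up to the 3-month survey where the 6-month survey is waived. List later urgent reports separately and keep them out of these rates.
3. Align the waivers in Sections 5.4 (6) and 5.7 (3), which differ on whether progression alone removes the 6-month survey, and correct the sentence in 5.4 (1) that literally excludes that survey.

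This costs wording only, with no extra visit or form.

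If the full treatment period is wanted instead, add Grade 3 or higher adverse event items (name, worst grade, onset date, as Section 19.1 (2) requires) to the existing annual survey. The price is a few EDC fields and a recall period of up to 12 months, which should be stated with the results.

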#### (2) Adverse events subjected to evaluation

Medical treatment and examination of subjects in this study is conducted within the normal range of regular clinical practice. Therefore, the risk of adverse events in subjects who participate in this study is similar to that in regular clinical practice. For this reason, information about adverse events of Grade 2 or milder is not collected in this study. Clinical investigators record the name, most severe grade, and date of initial development of the adverse events in a "Progress report" (Appendix X) for adverse events of Grade 3 and more severe. The naming of adverse events and their grades is determined based on the CTCAE v4.0.

#### (3) Handling of treatment-related death

In a case of treatment-related death, causal adverse events are defined as Grade 5. In addition, treatment-related death cases are urgently reported {19.2 (1)}. The final grades of causal adverse events are determined based on *ex post facto* examination including the urgent report.

### 19.2 Reporting of adverse events

When adverse events carrying an obligation to report corresponding to the below categories occur, a principal investigator reports to the secretariat. In addition, if serious adverse events ("serious" specified in ICH E2A) for which a causal correlation with the study treatment cannot be negated are observed, a report as stipulated by the reporting system of safety information on drugs etc. {Pharmaceutical and Medical Device Act, Section 68 (10), Reports of side effects} are appropriately implemented by the principal investigator's own responsibility in accordance with the procedures

stipulated by each medical institute.

(1) Adverse events carrying an urgent obligation to report

Adverse events corresponding to any of the following must be urgently reported via an "Emergency adverse event report" (Appendix X). These adverse events are defined as "Major adverse events".

① All deaths occurring during the study endocrine therapy.

② Deaths within 30 after the final administration of the study endocrine therapy and all deaths before the initiation of the next treatment.

"30 days" means 30 days counted from the day following a treatment day (the treatment day is defined as Day 0). All deaths occurred during this period are urgently reported regardless of the suspected causation.

However, even deaths occurring in a period other than the above (i.e., more than 30 days after the final administration of the study endocrine therapy and after the initiation of subsequent treatment) must be urgently reported when a correlation with the study endocrine therapy is suspected.

③ Unknown non-hematotoxicity observed before the initiation of the next treatment

(2) Adverse events carrying a regular obligation to report

Adverse events carrying a regular obligation to report are defined as any adverse events corresponding to Grade 3 or Grade 4 that are not adverse events carrying an urgent obligation to report {19.2 (1)}.

(3) Principal investigators' obligation to report and reporting procedures

① Urgent report

When adverse events occur that carry an urgent obligation to report {19.2 (1)}, a clinical investigator must immediately inform the relevant principal investigator. When the principal investigator is not available, the clinical investigator must cover the responsibility of the principal investigator.

When an adverse event subjected to urgent reporting is observed, the event must be orally reported to the secretariat within 24 hours and the principal investigator must complete an "Emergency adverse event report" (Appendix X) (It is also acceptable to use a form provided by the hospital) and submits a [contact]) or E-mail ([[contact]](mailto:[contact])) to the CSPOR data center within 72 hours after knowing the incidence of the adverse event.

In addition, the principal investigator must prepare a case report (A4 size, free format) describing further information as a separate document and submit a fax to the CSPOR data center within 15 hours after knowing the incidence of the adverse event.

② Regular report

Principal investigators should record predefined terms in the "Progress report" (Appendix X) corresponding to the timing of the incidence of the adverse events and submit it to the CSPOR data center at the stipulated normal submission time of the Progress report.

